### Statistical analyses

Missing data will be imputed so that all participants will be included in the analyses, and using LISREL 8.8, the multiple imputation will be carried out by the expectation maximization algorithm [37]. Both an intention to treat as well as a completer analysis will be performed.

In order to examine the effectiveness of FG-c overall effectiveness will be examined for all outcome measures by conducting an ANCOVA, with the outcome measures at post-test as dependent variables, treatment condition as factor and pre-intervention scores of the outcome variables as co-variates, as is recommended for RCTs using pre- and post-tests [38]. Effect sizes will be computed as Cohen’s d, based on adjusted means and standard errors.

For categorical moderator analyses, the same ANCOVA’s will be conducted, with the moderators as factor. Post-hoc analyses for moderator effects will be conducted by splitting the file according to the moderator and again conducting an ANCOVA and calculating effect sizes separately for each group. Regression analyses will be conducted for the continuous moderators.

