### Study sample

We aim to include *N* = 300 families, who will be randomized in a 2 (FG-c): 1 (control group) ratio to ensure that there is enough power to also conduct the planned moderator analyses. These groups are large enough to detect effects of FG-c’s.

Given the goal of YCAA to carry out 800 FG-c’s each year, the inclusion of 300 families will be completed within six months. This sample size is sufficient to test the hypotheses with an alpha of .05 and a small to medium effect (*d* = .35). FG-c can be used for all families, so there are no exclusion criteria in this study.

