Additionally, a rich set of instruments will be used, so that if there is any effect on any of the outcomes, there is a large likelihood to identify this effect. Moreover, potential moderators in terms of program as well as participant characteristics will be examined, so that the present study will provide information on when and for whom FG-cs are most likely to be effective. Program integrity will be examined and fulfillment of each phase of FG-c will be registered. Finally, the cost-effectiveness of FG-c will be examined: valuable information for both politicians as well as families who invest time in a FG-c.

However, there are also several limitations, which may threaten the value of our study. First, there is a risk in having this many informants and assessment moments (5 time points). There is the risk that the families or other informants will drop out of the study. We will put a lot of effort in maintaining the families in the study. Thankfully, the research group has experience with motivating for and retaining participants in research [39], but this always needs full attention.

Additionally, TAU in the control group may cause smaller effect sizes when compared to no treatment in the control group. However, as the research question is whether FG-c adds something to the usual child care services, this is the most logical design.

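### The planned multiple imputation is specified as the EM algorithm, which alone gives one completed data set; the ANCOVA then treats filled-in scores as observed, with an error whose form and size depend on an unstated imputation model and missing-data rate

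*Protocol article*

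**What the plan says.** The Statistical analyses section of the protocol sets the aim: "Missing data will be imputed so that all participants will be included in the analyses". It then gives the means, with LISREL 8.8 as the software: "the multiple imputation will be carried out by the expectation maximization algorithm". The analysis of every outcome is an ANCOVA of the post-test score with "treatment condition as factor and pre-intervention scores of the outcome variables as co-variates". On effect sizes it says: "Effect sizes will be computed as Cohen’s d, based on adjusted means and standard errors". Two analysis sets are planned: "Both an intention to treat as well as a completer analysis will be performed".

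The section does not mention several completed data sets, random draws, pooling or any variance correction. It does not say which variables enter the imputation. No missing-data rate is given anywhere; the Discussion says only "There is the risk that the families or other informants will drop out of the study".

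**The concern.** Multiple imputation and the EM algorithm are different things. EM converges to one set of maximum-likelihood means and covariances, and filling the gaps from it gives one completed data set. Multiple imputation needs repeated draws that carry both residual and parameter uncertainty, followed by pooling. The protocol puts the label of one on the algorithm of the other.

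A number of imputations or a pooling rule could be left to a statistical analysis plan. The difficulty here is that the article does name a method, and that method, taken as written, leads to a wrong result. An ordinary ANCOVA on 300 completed records counts filled-in scores as data. Depending on the imputation model, the harm falls either on the standard errors and p-values or on the size of the treatment effect. The same ANCOVA serves all outcomes, including child safety, and the categorical moderator analyses.

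**Working it through.** **Inputs from the protocol.** 200 FG-c and 100 control families (Design); alpha .05 and d = .35 (Study sample); ANCOVA adjusted for the pre-test (Statistical analyses).

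**Assumptions.** Two-sided test; values missing at random with respect to everything, equally in both arms; correlation between time points .5, with .6 as a check; share missing at the post-test m = 5% to 40%.

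**The plan's own figure.** With complete data the standard error of the difference in SD units is √(1/200 + 1/100) = 0.1225. Then .35/0.1225 = 2.86, and power is about Φ(2.86 − 1.96) = 0.815. The protocol states no power; 80% would need 97 + 194 = 291 families. So N = 300 is reproduced, and the sample-size statement is not affected by this point.

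**Case A: condition is in the imputation model, gaps filled with conditional means.**

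1. Filled-in points lie on the fitted regression surface, so the estimate equals the one from the observed families. With residual SD s, its true SE is about s·√[(1/200 + 1/100)/(1 − m)].
2. The ANCOVA spreads the same residual sum of squares over 300 families. Its residual SD is about s·√(1 − m), and it uses the nominal group sizes. Reported SE ≈ s·√(1 − m)·√(1/200 + 1/100).
3. The ratio of reported to true SE is therefore about 1 − m, and type I error ≈ 2[1 − Φ(1.96(1 − m))].
4. Example: correlation .5 gives s = √(1 − .25) = .866. At m = .20 the true SE is .866 × .1225/√.8 = .119 and the reported SE is .866 × .1225 × √.8 = .095. Simulation gave .120 and .095.

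Type I error, formula and simulation:

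| Missing | Formula | Simulated, r = .5, pre-test only | Simulated, r = .5, intermediate assessments also used | Simulated, r = .6 | Further run, r = .5 |
|---|---|---|---|---|---|
| 5% | 6.3% | – | – | – | 6.7% |
| 10% | 7.8% | 8.1% | 7.5% | 8.6% | 7.6% |
| 20% | 11.7% | 12.2% | 10.0% | 11.9% | 11.4% |
| 30% | 17.0% | 16.0% | 15.4% | 16.6% | 17.5% |
| 40% | 24.0% | 23.4% | 21.0% | 24.5% | 24.3% |

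The first two simulation columns use 2,500 null trials per cell and the r = .6 column 6,000. With 2,500 trials the Monte Carlo error at 16% is √(.16 × .84/2500) = 0.7 percentage points. The ratio of reported to true SE at 10/20/30/40% missing was 0.89/0.79/0.70/0.60 with the pre-test only, and 0.90/0.83/0.73/0.64 with the intermediate assessments.

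Adding one random residual to each filled-in score does not cure it. At r = .5, type I error at 10/20/30/40% missing was 7.0/10.9/13.6/17.1% with the pre-test only, and 6.8/9.2/12.6/15.4% with the intermediate assessments.

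**Case B: condition is left out of the imputation model.** Filled-in scores then carry no group difference beyond what the other assessments carry. With the pre-test only, the estimate shrinks to about (1 − m) of its value: .8 × .35 = .28 at 20% missing. Simulation gave .279, and .303 when the intermediate assessments were used. Type I error at 20% missing was 5.4% and 4.7% respectively. With the pre-test only, power was almost that of the observed-data analysis (83.3% against 83.7%), so the harm lies in the estimated effect and its interval rather than in the test.

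**Check of the remedy.** At 30% missing, 500 null trials, 20 bootstrap-EM imputations with residual noise and condition in the model, pooled by Rubin's rules: ratio of mean SE to empirical SD 1.01, type I error 4.6%. In the same trials a single EM conditional-mean fill gave 0.74 and 15.2%, and one random draw gave 0.78 and 12.0%.

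**The case against.** The strongest reply is that the protocol says multiple imputation, cites a source for it, and never says that a single data set is analysed. The number of imputations and the pooling rule may stand in an analysis plan that is not shown. EM combined with bootstrapping and pooling would be genuine multiple imputation. This stands as a limit: a single data set is inferred from the algorithm named, not stated. It does not remove the point, because nothing in the text indicates such a scheme and the sentence as written names a method that does not produce it.

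Second, a reader might infer that standard errors and p-values are bound to be too small. The document does not support that, because it does not say whether condition enters the imputation. Without it, type I error stays near 5% and the fault is attenuation.

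Third, the size depends on a rate the protocol does not give, and family dropout need not mean missing safety scores. According to the Primary outcomes section, family managers complete the LIRIK and the safety line as standard agency practice. A uniform 20–40% across outcomes would be unsupported. This stands, which is why the range starts at 5%.

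Fourth, a completer analysis is also planned. If that means families with observed scores, it would be free of this particular error. It does not repair the imputed analysis.

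A reader might also take dropout to be the authors' main threat, or the intention-to-treat analysis to be the main one. The Discussion only lists dropout first among the limitations, and the Statistical analyses section ranks neither analysis above the other.

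**Conclusion.** The point holds in a conditional form. What is secure is the mismatch: EM alone gives one completed data set, and an ordinary ANCOVA on it ignores the uncertainty of the filled-in scores.

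The consequence depends on what the protocol leaves open:

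- **Condition in the imputation model:** type I error at nominal 5% is about 6–7% at 5% missing, 7–9% at 10%, 10–12% at 20% and 14–17% at 30%. Standard errors are understated by up to about the missing share. A single random draw that also uses the intermediate assessments falls slightly below these ranges.
- **Condition left out:** type I error is near 5%, but d = .35 becomes about .28–.30 at 20% missing.

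These figures assume values missing completely at random and a correlation of .5 to .6 between assessments. The harm is slight at 5% missing and serious from about 20%. Since effect sizes are to be computed from the standard errors, an understated SE would also carry into Cohen's d. The plan is faulty in either case, so the sentence needs correcting whatever the eventual dropout.

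**What to change.** Replace the EM sentence with proper multiple imputation:

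- MCMC, chained equations or bootstrap-EM, with at least 20 data sets;
- an imputation model that contains condition and all time points at which each measure is collected;
- the planned ANCOVA run in each data set, with results pooled by Rubin's rules.

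The model should follow Table 1 measure by measure: the CAPI is listed at T1, T3 and T5, the LIRIK has no T2, and the Succint safety score has no T1. Whether a conference took place is recorded only in the FG-c arm, so it cannot simply be added as a predictor for all families.

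Alternatively, for measures with repeated assessments, fit a likelihood-based mixed model to the observed scores without imputation. This changes the planned ANCOVA and is not needed to correct the fault. If a pooled bootstrap-EM scheme was intended all along, a sentence saying so, with the number of imputations and the imputation model, is enough.

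No change to sample size, data collection or procedures is needed. The cost is revised wording, a little more analysis work, and intervals that are wider but correct.

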## Methods and design

The study aims to answer two main questions. The first question is whether Family Group conferences in youth care are effective as a decision making model in terms of increased child safety, involvement of the social network, perceived control over problems and a reduction in use of professional care. In order to determine the effectiveness of FG-cs, a RCT will be carried out including 300 families referred to Youth Care Agency Amsterdam (YCAA). Moreover, costs associated with FG-c will be identified in order to determine the cost-effectiveness of FG-cs.

The second research question concerns the moderators of the effectiveness of FG-c. Both participant and program characteristics will be examined as potential moderators. Program characteristics to be examined are program integrity and characteristics of FG coordinators and family managers (responsible for supporting the implementation of the FG plans developed by the broader social network of the family). It is crucial to examine program integrity (i.e., the extent to which different phases of a FG-c have been conducted according to the protocol). Without having established program integrity, there is the risk of concluding that FG-cs are not effective, whereas in fact the FG-c has not been fully implemented. Furthermore, it is possible that a successful FG-c has taken place, but the plan developed in the FG-c has never been carried out. It is therefore important to determine whether all stages of the FG-c have been implemented as planned.

Additionally, it is important to examine family characteristics as potential moderators of the effectiveness of FG-c. It is plausible that FG-cs are not equally effective for every participating family. For example, families with a small social network, or with limited possibilities to attend a conference or with other particular characteristics that hamper the organization or carrying out of a FG-c or the FG plans are less likely to attend a FG-c. Identifying those families who are less likely to fulfill an FG-c may result in savings.

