### Design

A randomized Controlled trial will be conducted to examine whether FG-cs are effective in changing: (1) child’s safety (i.e., decrease in (risk for) abuse/neglect; less supervision orders or shorter supervision order; less or shorter out of home placement); (2) the involvement of the broader social network; (3) perceived control over the problems in the families, empowerment of parents; improvement of family functioning; (4) less use of professional care. A second aim is to study whether the effectiveness of FG-c is influenced by characteristics of the implementation of the methodology, characteristics of the family managers (such as education, or attitude towards FG-c), or by family characteristics (such as size of the social network, ethnicity or family type: single/married).

Using computerized randomization two comparable groups will be formed. Until the inclusion of 300 families is completed (presumably within 6 months), every family starting care at Youth Care Agency Amsterdam (YCAA) will be randomly allocated to care with or without a Family Group conference. Because allocation to care with a FG-c will not always result in an actual Family Group conference and/or an approved Family Group plan, 200 families will be assigned to care with FG-c and 100 families to care without FG-c. Five multi-informant/source (parent, family manager; FG-coordinator; member of the family’s social network; child (if > 8 years of age), and file analysis) assessments will be carried out in both groups. Pre-tests will take place before FG-cs starts. Subsequently, in both groups post-tests will be carried out 1, 3, 6 and 12 months after the FG-c has taken place (see also Figure 1 for the flow chart).

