**Figure 1 F1:**
[figure not shown]
Randomization procedure.

In addition, for families in the FG-c condition, it will be assessed (1) whether a FG-c coordinator explained the concept of a FG-c; (2) whether an FG-c has taken place, (3) whether a plan has been formulated; and (4) whether the plan has been carried out (at the moments when posttests at 1, 3 and 6 months after the FG-c have been carried out). To diminish the burden that is imposed on families as much as possible, measurements at 1 and 3 months will be done as much as possible by telephone.

The design of this study is approved by the independent Ethical Committee of the Faculty of Social and Behavioral Sciences of The University of Amsterdam (approval number: 2013-POWL-3308).

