## Discussion

The implementation of Family Group-conferencing for decision making in child welfare has gained popularity rapidly. In The Netherlands, a change in youth protection is proposed for 2015 according to which the law states that every family has the right to start child care with making their own plan. The philosophy of a society in which everyone can participate and has the right to make its own decisions is the background of this development. Question is, however, if every family is able to make its own plan, and if these plans are effective in terms of increased child safety, increased commitment of the social network, if families are able to gain control over their own help, if family functioning improves and use of professional care decreases. The present study addresses this by examining the effectiveness of FG-c by means of a randomized controlled trial. Worldwide, despite an overload of studies examining FG-c [16], there are only six studies that examined FG-c with a comparable comparison group [15]. It is thus of crucial importance to conduct a RCT of FG-c, including sufficient participants as the present study intends to achieve.

Moreover, few RCTs have been conducted of FG-c, even less so examine for whom, under what conditions FG-c is likely to be most effective, as the present study does by carefully examining implementation, method and participant characteristics.

The present study thus has several strenghts: several strengths: it will extend the knowledge on Family Group-conferencing as a decision making procedure in child care. By using a randomized controlled trial, confounding variables are excluded as much as possible. A sufficiently large sample size will be used to study effectiveness as well as moderators of the effectiveness.

Moreover, a multi-informant approach will be used by asking parents, family managers, FG coordinators, a member of the network and children (if older than 8) to report on the outcomes and by conducting file-analysis.

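### The 2:1 ratio does not offset non-uptake of conferences under intention to treat, N = 300 carries no stated allowance for it, and the completer analysis is left undefined

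*Protocol article*

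**What the plan says.** The Design section of the protocol article gives the reason for unequal allocation: because "allocation to care with a FG-c will not always result in an actual Family Group conference and/or an approved Family Group plan, 200 families" go to FG-c and 100 to control. The Study sample section gives a second reason for 2:1, power for the moderator analyses. It calls N = 300 "sufficient to test the hypotheses with an alpha of .05 and a small to medium effect", with d = .35. It does not state a power, an expected uptake, or whether .35 refers to all allocated families or only to those who have a conference.

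The text after Figure 1 says that "for families in the FG-c condition, it will be assessed (1) whether a FG-c coordinator explained the concept of a FG-c", and then whether a conference took place, whether a plan was made and whether it was carried out. The opening of Methods and design names families less likely to attend: "families with a small social network, or with limited possibilities to attend a conference", among others.

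Under Statistical analyses, straight after the sentence on imputing missing data, the plan says: "Both an intention to treat as well as a completer analysis will be performed". Completer is not defined there or elsewhere, and neither analysis is called primary.

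**The concern.** The plan foresees non-uptake and responds by enlarging the FG-c arm at the expense of the control arm. That does nothing for the intention-to-treat contrast: families without a conference stay in the FG-c arm and pull its mean towards control, however many families the arm holds. For a fixed total, moving away from equal arms also costs precision.

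Two things are at stake. First, the statement that the sample is sufficient may hold for one meaning of d = .35 and fail clearly for the other. Second, if intention to treat turns out diluted and inconclusive, the completer analysis may be read as the effect of an actual conference. If it keeps only FG-c families who held one and compares them with every control family, it removes families with small networks or little opportunity to attend from one arm only. Social support is itself a secondary outcome, so that selection lies close to what is measured.

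**Working it through.** **Inputs.** From the documents: N = 300, 200 FG-c and 100 control, alpha .05, d = .35. Assumed because not stated: two-sided test, 80% target power, equal SDs, no effect in FG-c families without a conference, no conferences in controls, and uptake u between 50% and 100%.

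**1. Reproducing the plan's figure.** With SD = 1 and twice as many FG-c families as controls, the number of controls needed is (1.96 + 0.84)² × (1 + 1/2) / 0.35² = 7.85 × 1.5 / 0.1225 ≈ 96.1, so 97. With 194 FG-c families the total is 291. The planned 300 therefore matches about 80% power for d = .35 with no reduction for non-uptake.

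**2. Standard error by ratio.**
- 200:100: √(1/200 + 1/100) = 0.1225
- 150:150: √(1/150 + 1/150) = 0.1155

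The 2:1 standard error is about 6% larger. The smallest effect detectable with 80% power at 200:100 is 2.80 × 0.1225 = 0.343.

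**3. Dilution.** If .35 is the effect of a conference that takes place, the intention-to-treat effect is u × .35. The ratio does not enter. Power is Φ(u × .35 / SE − 1.96); the opposite tail is negligible. The last column multiplies the SE by √(1 − .5²) = 0.866, crediting ANCOVA with an assumed baseline correlation of .5 (d in raw SD units).

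| Uptake | Diluted d | Power 2:1 | Power 1:1 | Power 2:1, ANCOVA r = .5 |
|---|---|---|---|---|
| 100% | .35 | 81.5% | 85.8% | 91% |
| 90% | .315 | 73.0% | 77.9% | 84% |
| 80% | .28 | 62.8% | 67.9% | 75% |
| 70% | .245 | 51.6% | 56.4% | 64% |
| 60% | .21 | 40.3% | 44.4% | 51% |
| 50% | .175 | 29.8% | 32.8% | 38% |

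The noncentral t gives the same picture (81.3% against 85.6% at full uptake, 62.5% against 67.6% at 80%). At every uptake shown, 2:1 is 3 to 5 points below 1:1 without adjustment. Without adjustment, 80% power is kept only down to u = .343/.35 ≈ 98%.

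**4. Conference effect needed for 80% power.** Unadjusted, .343/u: .43 at 80% uptake, .57 at 60%, .69 at 50%. With r = .5, .297/u: .37, .50 and .59.

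**5. Selection bias, only if completers are conference families set against all controls.** Suppose families with and without uptake would differ by g SD in outcome if neither had a conference. With no true effect, the expected difference between completers and controls is (1 − u) × g, with SE √(1/100 + 1/(200u)). No value of g is in the documents.

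| Uptake | g | Bias (SD) | Type I error |
|---|---|---|---|
| 80% | 0.3 | 0.06 | 7.6% |
| 80% | 0.5 | 0.10 | 12.3% |
| 50% | 0.3 | 0.15 | 18.5% |
| 50% | 0.5 | 0.25 | 42.4% |

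Baseline adjustment reduces this bias only as far as the baseline score captures what drives attendance.

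**The case against.** **The effect size.** The plan compares families allocated to care with or without FG-c, so .35 can fairly be read as the effect in the allocated arms. On that reading N = 300 is adequate, at about 81% power. This stands. A reader might infer that the trial is underpowered; the documents do not establish that, because they do not say which effect .35 is.

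**The ratio.** The plan nowhere claims that 2:1 restores intention-to-treat power, and several moderators (network members present, time to the conference, phases followed) exist only in the FG-c arm, where 200 families serve better than 150. This also stands and is a sound reason for 2:1. It does not rescue non-uptake as a reason. Even for conference families against all controls, leaving bias aside, 2:1 falls short of 1:1 at 80% uptake (78.4% against 81.5%), equals it at 50% (69.7%) and gains only below that (64.6% against 63.0% at 40%).

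**The completer analysis.** It is tempting to say that the plan sets self-selected FG-c families against all controls. The text does not say so. The sentence follows the one on missing data, and the Discussion worries about drop-out, so completer may simply mean families in both arms who completed the assessments, a usual check on an imputed analysis. The other reading has some support, since imputation is meant to keep all participants in and stages are recorded only for FG-c families, but it remains an inference. The same sentence also plans intention to treat.

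**Conferences among controls.** A reader might infer contamination from the Discussion's remark on a change proposed for 2015, under which "the law states that every family has the right to start child care with making their own plan". That is speculative: the change is only proposed, no recruitment dates are given, control plans are made by the family manager with the parents, and file analysis covers both groups.

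**Conclusion.** The point holds in limited form. Expected non-uptake is not a valid reason for 200:100 if the aim is the intention-to-treat comparison: the ratio leaves the diluted effect unchanged and costs 3 to 5 points of power against equal arms. This follows from arithmetic and does not depend on knowing the uptake.

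The sufficiency statement is conditional. It holds if .35 is already the effect across all allocated families. If .35 belongs to conferences that take place, power is 63% at 80% uptake and 40% at 60%, or 75% and 51% with an assumed r = .5. Uptake, sidedness, target power and r are all assumptions.

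The risk from the completer analysis is conditional too. It arises only under the conference-completer reading, and the bias figures illustrate a mechanism under assumed differences; they do not predict this trial's error rate. What is certain is that the term is undefined and that neither analysis takes precedence. This should be put right before results are seen, but it does not invalidate the trial.

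**What to change.** 1. Name intention to treat as the primary analysis, and define completer. If it means assessment completers in both arms, say so and keep it as a check on the imputation.
2. In place of any comparison of conference completers with all controls, estimate the effect of receiving FG-c as a complier-average causal effect, with allocation as instrument, conference held (yes/no) as exposure and T1 covariates. State the exclusion assumption that allocation acts only through the conference. The Conditions section describes an activation phase before the conference, in which the coordinator already contacts family and network, so add a sensitivity analysis that counts the start of that phase as exposure.
3. In Study sample, state that d = .35 is the diluted intention-to-treat effect, and give the conference effect that N = 300 could detect over a range of uptake (about .343/uptake unadjusted).
4. In Design, drop non-uptake as a justification for 2:1 and keep the moderator reason.

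The cost is one extra model, whose confidence intervals will be wider than those of a naive completer comparison, and a less favourable sample-size sentence. Neither the number of families nor the allocation need change.
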